#### Potential sources of bias

There are potential sources of bias in our study that may include selection bias due to the criteria for participant inclusion and performance bias related to the intervention delivery. To mitigate these biases, we will employ randomization for participant allocation and ensure that the intervention is administered by trained personnel who remain blind to group assignments. Additionally, we will conduct regular monitoring to ensure adherence to the protocol and minimize any deviations.

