### IVR stimulation (IVR)

The intervention will be programmed once a day (preferably in the morning) for three consecutive days (including weekends), lasting approximately 4 min. Two ad-Hoc 3D videos, produced by Nautilus Enterprise (Pamplona, Navarre) will be available for this purpose. On the 1st and 2nd day, one of the videos is reproduced through the HMD. On the 3rd day of the intervention, the patient will decide which video to watch.

The first video has two different natural settings: (a) Irati Forest; (b) Bardena desert. The second video is a simulation of visiting villages and cities of Navarre, going by car through landscapes, squares with people walking, iconic buildings, and ending with a drone view of a small village. Both the 3D videos were developed in the Navarre region, with the aim of making the stimulation familiar to most of the patients. The videos were recorded using 6 cameras (Insta Pro 2, Shenzhen, Guangdong, China); afterwards, Nautilus Enterprise performed image stitching, editing, colorization, sound, and rendering of the video. The final export was performed at a quality of 5760 × 2880, with a data transfer rate of 80 MB/s. A Matrice drone (Shenzhen, Guangdong, China) was used for the drone video. Regarding the vehicle used for some parts of the videos, considering carbon footprint, an electric car was used, trying to reduce to the minimum the ambient impact.

The research staff will continuously supervise the intervention sessions. For safety reasons, patients will seat in armchair during the stimulation, and he/she will never stand up. A daily record will be documented. The participants and their family members or caregivers will be familiarized with the IVR and the procedure before starting the intervention. To make it easier and more feasible the VR session, it will be performed in own patients’ hospital room. Figure 2.

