Completed personal data or other documents containing protected personal health information will be stored in a locked file at the principal investigator’s office. The data will be entered into an electronic de-identified database authorized by a study team member and checked for completeness and accuracy. Access to data using identifiers is strictly restricted by authorized study team members and authorities. Electronic data will be securely stored on a server regulated by a local research institute (NAVARRABIOMED). Any identifiable data will be maintained until consent is revoked. The times at which different variables will be measured are listed in Table 3 (outcome variables will be assessed by dedicated medical staff).

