#### Randomization and blinding

All patients hospitalized in the AGU will be screened for the eligibility criteria. The ones who meet the eligibility criteria will be randomly assigned to one of the IG or to the CG within the first 48 h of admission, following a simple randomization procedure in a 1:1:1:1 ratio without restriction. Randomization will be performed using the randomizer software (https://randomizer.org/) with a random permuted block design with block sizes.

Participants will be explicitly informed and reminded not to discuss their randomization assignment with the assessment staff. The assessment staff will be blinded to the participants’ group and the main study design. It is not possible to mask the group assignment to the staff involved in the IG training. Patients and caregivers/legal guardians (in case the patient has cognitive impairment) will be informed of their random inclusion in one group but will not be informed on the group in which they are. Figure 3.

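### The bias section claims blinded delivery of the intervention, which the randomisation section says is impossible; patients are not effectively masked either

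*Protocol article*

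**What the plan says.** Three sets of statements in the protocol article bear on who is masked.

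- **Staff who deliver the intervention.** Potential sources of bias names "performance bias related to the intervention delivery" as a threat. Among its mitigations it undertakes to "ensure that the intervention is administered by trained personnel who remain blind to group assignments". It also lists randomisation and regular monitoring of adherence. Randomization and blinding says: "It is not possible to mask the group assignment to the staff involved in the IG training".
- **Patients and caregivers.** Randomization and blinding says they know that they were randomised to a group but "will not be informed on the group in which they are". The same section says: "Participants will be explicitly informed and reminded not to discuss their randomization assignment with the assessment staff". The IVR section adds: "The participants and their family members or caregivers will be familiarized with the IVR and the procedure before starting the intervention". The exercise section says the same of the cycle ergometer.
- **Outcome assessors.** Randomization and blinding masks the assessment staff to group and to the main study design. The data-handling paragraph that closes the secondary outcomes says that "outcome variables will be assessed by dedicated medical staff", without saying whether these are the masked assessors.

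**The concern.** The two statements about delivery staff cannot both be true, and the wrong one is offered as protection against performance bias. A reader who relies on the bias section would credit the trial with a safeguard that another section rules out.

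Who is masked decides how the outcomes can be read. Of the three primary outcomes, MMSE and HABAM are rated by an assessor, and handgrip depends on the effort the patient makes. The Geriatric Depression Scale, the anxiety inventory, the EQ-5D and its visual analogue scale are the patient's own report. If patients know what they received, expectation and encouragement can move the effort-dependent and self-reported measures even when the assessor is masked.

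There is also a possible route through co-treatment. Under Description of interventions and usual care, geriatricians may offer physiotherapy in any group as they judge necessary, and the article describes no masking of these clinicians.

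**Working it through.** The plan gives no figure on this point, so the check sets the statements side by side.

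**Step 1: are the two sections about the same people?** The bias section speaks of the personnel who administer the intervention. The randomisation section speaks of the staff involved in the training of the intervention groups (IVR, ME and IVR + ME). Both describe those who run the sessions.

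**Step 2: which statement fits the described conduct?** The IVR section says: "The research staff will continuously supervise the intervention sessions". The exercise section repeats this. A session consists of watching a video through a head-mounted display, or of resistance exercises and a cycle ergometer. The Control Group section gives usual care and describes no sham headset or attention control. A staff member who runs a session therefore sees that the patient is in an intervention group, and sees which component is being given. The randomisation section is right and the bias section is wrong as written.

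**Step 3: what is left of the bias section's mitigation?**

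| Safeguard listed | Does it act on performance bias? |
|---|---|
| Randomisation | No. It balances the groups at allocation and does not govern what happens afterwards. |
| Blinded delivery | Not available (step 2). |
| Monitoring of adherence | In part. It can limit deviations in delivery but not the effects of knowing the arm. |

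Assessor masking, stated elsewhere, acts on detection bias. It is a separate safeguard, and this contradiction leaves it untouched.

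**Step 4: are patients masked?** A request not to discuss one's assignment has a purpose only if the patient can know something about it. A patient shown the headset or the ergometer beforehand, and then treated with it on three days, knows what was received. Withholding the formal group label does not change that.

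**Step 5: does the plan unmask the assessors?** The secondary outcomes include the Simulator Sickness Questionnaire, the System Usability Scale, and satisfaction and enjoyment records. These have meaning only for patients who had a session. The article does not say who collects them. If masked assessors did so before testing MMSE, handgrip or HABAM, they would learn whether the patient was in an intervention group or a control. The text shown establishes neither who gives the forms nor in what order, so this step identifies a gap to close and not a demonstrated breach.

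**The case against.** The strongest defence is that the section governing blinding is candid. It says session staff cannot be masked and it keeps assessor masking, so the sentence in the bias section may be a slip that meant the assessors. Open delivery is unavoidable with these interventions and is not a design fault. That is fair, but it does not rescue the sentence. If assessors were meant, the sentence names the wrong people, and masking them would not address the performance bias it is offered against. It is also fair that only one of the listed safeguards fails, not all three.

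On patients, the wording could mean only that the formal allocation is not announced, with the reminder serving to protect the assessors. The consent forms are not shown, so what patients are told cannot be settled. This makes the statement awkward rather than false. It still cannot be read as masking.

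A reader might go further and infer that the plan itself breaks assessor masking: two IVR arms, 2 × 53 = 106 of 212 patients, would have VR-specific forms, and three intervention arms, 3 × 53 = 159 of 212, would have session-specific records, so the assessor would learn intervention or control status for everyone. The counts are correct, but the document does not support the premise. The outcome staff are called dedicated medical staff, not masked assessors. The forms are grouped with session-day records such as heart rate, oxygen saturation and falls during the intervention, which session staff could naturally complete. The assessment schedule is a figure that is not shown. The counts are therefore conditional and are not a measure of this problem.

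**Conclusion.** The point stands as a wrong statement about blinding. The claim of blinded delivery is contradicted within the article and is incompatible with the delivery described. The statement that patients are not informed of their group does not amount to masking. Only outcome assessors can credibly be called masked, and nothing shown contradicts that they are.

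This rests on two readings: that the personnel in one section are the staff in the other, and that controls receive no sham, which is how the control condition is described. The size of any bias cannot be derived from the document. No sample-size, power or analysis figure is affected. What changes is what the trial may claim about protection from performance bias, above all for handgrip effort and for self-reported mood and quality of life.

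**What to change.** 1. Under Potential sources of bias, delete the claim of blinded delivery. State that session staff, patients and caregivers are in effect unmasked and that only outcome assessors are masked. Acknowledge performance bias as a remaining limitation.
2. Under Randomization and blinding, replace the statement about what patients are told with one that does not imply masking. Keep the reminder not to reveal the assignment to assessors.
3. State that mood and quality-of-life results will be interpreted as unblinded self-report.
4. As a safeguard, specify that session staff, not masked assessors, collect the Simulator Sickness Questionnaire, the System Usability Scale, and the satisfaction and enjoyment records. If this is already the practice, one sentence saying so is enough.

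The cost is wording and, at most, a reassignment of forms among existing staff. No extra personnel, patients or analyses are needed.

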#### Strengths and limitations

This study presents several strengths, notably the innovative application of immersive virtual reality for cognitive stimulation, coupled with a comprehensive multicomponent physical exercise regimen. This dual approach specifically targets a vulnerable population, potentially enhancing both cognitive and functional outcomes. However, there are limitations to consider. The generalizability of our findings may be constrained by the specific context of a tertiary hospital setting, which may not reflect broader community settings. Additionally, individual variability in responses to the interventions could impact the overall effectiveness.

## Discussion

Frailty and cognitive impairment are common geriatric syndromes in hospitalized older individuals, especially among those with severe functional dependency. To date, no randomized clinical trial has been involving these patients in a cognitive and functional intervention - dispensed through IVR and/or ME -, with the final aim of reducing hospital-associated cognitive and functional decline. Although our research group has been working with older inpatients for over a decade using multicomponent and VIVIFRAIL prescriptions, we previously focused only on autonomous patients. An innovative aspect of this study is to target those patients who are commonly unable to follow a traditional training, including those affected by dementia and functional impairment. Another remarkable novelty of this study is the strict cooperation of an interdisciplinary team, (including physiotherapists, geriatricians, physical education doctors, nurses, engineers), to provide comprehensive care and to reduce the inter-generational digital gap.

If our hypothesis is accurate, this project has the potential to enhance physical and psychological well-being of patients with severe functional dependency hospitalized for acute conditions, through virtual reality and physical exercise. Furthermore, this trial will inform upon eventual adverse events that may occur during the use of IVR or while performing ME, as well as upon the usability and acceptability of technology in this population. This trial represents a novelty in the geriatric patients’ care and may pave the way for other innovative interventions in the future.

### Status of trial

The trial is registered at ClinicalTrials.gov, number of registration NCT06340282, 24th May 2024. The study will be implemented and reported in accordance with the Standard Protocol Items: Recommendations for Interventional Trials (SPIRIT) Guidelines.

## Data Availability

No datasets were generated or analysed during the current study.

## Abbreviations

ADL: activities of daily living
AGU: Acute Geriatric Unit
CAM: Confusion Assessment Method
CG: control group
CIRS-G: Cumulative Illness Rating Scale-Geriatric
GDS: Global Deterioration Scale
EQ5D-3-L: EuroQol 5-D 3-L
HABAM: Hierarchical Assessment of Balance and Mobility
HMD: Head-Mounted Displays
HUN: Hospital Universitario de Navarra
IG: intervention groups
IVR: Immersive virtual reality
ME: Multicomponent exercise
MMSE: Mini-Mental State Examination
RASS: Richmond Agitation-Sedation Scale
SSQ: Simulator Sickness Questionnaire
STAI: Short Form of State Trait Anxiety Inventory adapted to Spanish Geriatric Population
SUS: System Usability Scale
TMT-A: Trail Making Test-A
